## Abstract

**Background:**

Currently, a PET-CT is used to assess the need for extended field radiotherapy of para-aortic lymph nodes (PALN) in International Federation of Gynaecology and Obstetrics (FIGO) stage IB2, IIA2–IVA (locally advanced stage) cervical cancer. A small study established a sensitivity and specificity estimate for PALN metastases of 50% (95% CI; 7–93%) and 83% (95% CI; 52–98%), respectively. Surgical staging of PALN may lead to a higher diagnostic accuracy. However, surgical staging of para-aortic lymph nodes in locally advanced stage cervical cancer is not common practice. Therefore, a phase 2 randomised controlled trial is needed to assess its safety and feasibility.

**Methods/design:**

In addition to standard imaging (MRI or CT scan) with PET-CT, 30 adult women with FIGO stage IB2, IIA2–IVA cervical cancer will be randomised to receive either surgical staging or usual PET-CT staging. Administering extended field radiotherapy will be based on lymphadenectomy results for the intervention group and on the PET-CT results for the control group. Follow-up visits at 0, 3, 6, 9 and 12 months will assess health-related quality of life and progression-free survival.

Primary safety and feasibility outcomes of surgical staging will be assessed by calculating means with 95% confidence intervals for duration of surgery, number of complications, blood loss, nodal yield after para-aortic lymphadenectomy and treatment delay due to surgical staging. Secondary patient-centred outcomes on quality of life and first year survival will be documented and compared between the two groups. Estimates of sensitivity, specificity and negative and positive predictive values of MRI, PET-CT and surgical staging will be presented with 95% CI.. All analysis will be performed according to the intention to treat principle.

**Discussion:**

This study will assess safety and feasibility, expressed as the number and severity of complications, effect on quality of life and the treatment delay due to surgically staging para-aortic lymph nodes in locally advanced cervical cancer. It will provide insight in the diagnostic accuracy of the PET-CT and detection rate of missed (micro)metastases due to surgical staging. This information will be used to assess the necessity for a phase 3 study on the diagnostic accuracy of the PET-CT and surgical staging. If a phase 3 study is deemed necessary, current data can be used for sample size calculation of such a phase 3 study.

**Trial registration:**

Nederlands Trial Register/Dutch Trial Registry (www.trialregister.nl), NTR4922. Registered on 24 November 2014.

## Background

Cervical cancer is fairly rare in the Netherlands, with an incidence of approximately 700 new diagnoses each year or approximately 8.3 new diagnoses per 100,000 women per year in the Netherlands [1]. Staging is based on the International Federation of Gynaecology and Obstetrics (FIGO) staging system for cervical cancer. It uses clinical features and becomes increasingly inaccurate as the disease progresses, with accurate staging failure rates rising from 25% in FIGO stage I and II to 65–90% in stage IIIB [2]. The lymph node status of pelvic and para-aortic lymph nodes is, besides tumour stage, the most important prognostic factor for disease recurrence in cervical cancer [3]. Failure to detect metastases in these lymph nodes may lead to suboptimal treatment. Para-aortic lymph node (PALN) metastases are quite common in FIGO IIA patients with positive pelvic lymph nodes (16%), whereas solitary PALN are rare (0.8%) [4]. PALN metastases affect around 20% of all stage IB2–IVA, although other studies claim considerably higher rates up to 40% [4–7].

Patients with advanced stage cervical cancer (FIGO stage IB2, IIA2–IVA) are primarily treated with pelvic radiotherapy and concomitant chemotherapy. Para-aortic lymph node (PALN) status and a subsequent need for extended field radiotherapy is assessed using a positron emission tomography (PET) combined with computed tomography (CT) scan (PET-CT). PET-CT provides a higher sensitivity and specificity than magnetic resonance imaging (MRI) [8, 9]. However, for detecting PALN metastasis, PET-CT seems to have a sensitivity and specificity of 50% (95% CI; 7–93%) and 83% (95% CI; 52–98%), respectively [10]. This uncertainty and these broad confidence intervals are due to the fact that only one small study (*n* = 16) explicitly assessed the diagnostic accuracy of the PET-CT. So far, this study is the only study that compared the PET-CT results of para-aortic lymph nodes in cervical cancer to the gold standard of histology. More evidence on diagnostic accuracy of PET-CT in detecting PALN metastases is needed. Some intervention studies provide a part of these data as they include surgical staging and the PET-CT in advanced stage cervical cancer, such as the LILACS trial [11]. However, in the LILACS trial, surgical staging is only performed in PET-CT negative patients and not in PET-CT positive patients. This may be due to the fact that the PET-CT seems to have a sensitivity of 50% and specificity of 83%, thus possibly being false negative in half of all patients with PALN metastases while being false positive in 17% of all patients without PALN metastases, or due to the assumption that the specificity and positive predictive value of the PET-CT are already acceptable. Regardless, although missing a PALN metastases due to a false negative result may be more detrimental to survival than ‘overtreating’ patients due to a false positive result, the radiotherapy-induced complications can also have a negative impact on the quality of life of patients. In addition, the confidence interval surrounding the specificity of the PET-CT ranges from 52 to 98%, leading to a large uncertainty. As such, more evidence on both the sensitivity and specificity of the PET-CT is warranted..

Recent studies show that surgical staging not only validates the imaging results, but may also lead to a treatment modification in 20–40% of the patients with locally advanced cervical cancer compared to PET-CT results [2, 12–16]. Surgical staging, i.e. removing the para-aortic lymph nodes by performing a para-aortic lymphadenectomy, leads to a gain in diagnostic accuracy by allowing adequate histological evaluation of the retrieved lymph nodes. Additionally, the resection of enlarged positive lymph nodes may provide therapeutic benefit [2, 15–18]. Whether this is due to removing the bulk of the disease or ensuring the radiation field includes confirmed nodal disease, or both, is unclear.

The proportion of treatment modifications may depend on both the diagnostic accuracy of the PET-CT and a clinician’s experience with interpreting the PET-CT results and performing the surgical staging. The validity of detecting metastasis with surgical staging compared to standard diagnostics remains to be elucidated. Currently, PET-CT is the gold standard in the Netherlands when there is a suspicion of para-aortic lymph node metastases based on either clinical data, MRI or CT scan. In addition, surgical staging of PALN in locally advanced stage cervical cancer is not common practice. Therefore, a phase 2 trial to assess safety and feasibility is warranted.

The PALDISC (*P*ara-*A*ortic *L*ymphadenectomy *I*n advanced stage *C*ervical cancer) trial will assess safety and feasibility of surgical staging in locally advanced cervical cancer in the Netherlands. It will provide insight in diagnostic accuracy of the PET-CT and detection rate of missed (micro)metastases due to surgical staging. This information will be used to assess the necessity for a phase 3 study on the diagnostic accuracy of the PET-CT and surgical staging. If a phase 3 study is deemed necessary, current data can be used for the sample size calculations of such a phase 3 study.

## Methods/design

This study is a multi-centre randomised controlled phase 2 trial with 1 year of follow-up. The study is currently being conducted at the Radboudumc Nijmegen and Catharina Hospital Eindhoven in the Netherlands. A general overview of the study is presented in a SPIRIT flow diagram (Fig. 1).

**Fig. 1 Fig1:**
[figure not shown]
SPIRIT flow diagram

### Inclusion criteria

Women (aged ≥ 18 years) with FIGO IB2, IIA2, IIB, IIIA, IIIB and IVA cervical cancer from general and specialised hospitals for gynaecologic care in the Netherlands are eligible for randomization after meeting the following criteria:Age of 18 years or above;Histologically confirmed squamous cell, adenosquamous or adenocarcinoma of the cervix;FIGO stage IB2, IIA2, IIB, IIIA, IIIB and IVA, staging performed by examination under anaesthesia;Fit for surgery;WHO-performance 0-2;WBC > 3.0 × 109/L, platelets > 100 × 109/L, creatinine clearance > 60 ml/min;Chest CT or X-ray, abdominal MRI or CT scan and PET-CT with no evidence of distant metastasis (PET positive > 2 cm);Written informed consent.

### Exclusion criteria

A potential subject who meets any of the following criteria will be excluded from participation in this study:Previous malignancy (except for non-melanoma skin cancer)Prior retroperitoneal surgeryPrevious pelvic or abdominal radiotherapyUpper abdominal intraperitoneal disease or evidence of ovarian metastasisEvidence of distant metastasis on imaging or physical examinationBulky para-aortic lymph nodes > 2 cmPregnancyOtherwise unfit for surgery

### Randomisation, blinding and treatment allocation

After providing informed consent, all patients will be randomised by the enrolling clinician using the randomization program provided by Castor EDC. Patients will be randomised equally between surgical staging and standard treatment using a permuted block design per centre; the allocation sequence itself is concealed from the patient, investigator and clinician [19]. Blinding of the patient, investigator and/or observer from the allocation result is not possible.

### Intervention, surgical procedure and histological analysis

Figure 2 shows the patient flow. Patients in the intervention arm will receive surgical staging of PALN, besides the regular treatment and imaging (including PET-CT) of locally advanced stage cervical cancer. This will be a laparotomic, laparoscopic or robot-assisted node by node para-aortic lymphadenectomy from the common iliac bifurcation up to the left renal vein, performed by an experienced team of retroperitoneal surgeons. In case of a laparoscopic or robotic procedure, the surgeon may choose between trans- or peritoneal approach. All open procedures should be based on a retroperitoneal approach due to reported increased morbidity [15, 20–22]. A sentinel node procedure, as well as a debulking of bulky pelvic nodes, and an ovarian displacement to avoid radiotherapy on an ovary may be performed optionally.

**Fig. 2 Fig2:**
[figure not shown]
Patient flow

Histological analysis of PALN will be performed node by node and includes all normal procedures with an additional assessment on lymph node yield, node diameter and diameter of micro metastases. Patients with metastatic PALN on histological analysis will receive extended field radiation therapy with concurrent chemotherapy and optional adjuvant chemotherapy. To ensure a comprehensive assessment of the primary tumour, nodal sites and potential metastatic sites, a physical examination including a rectovaginal examination under anaesthesia and radiology including a chest CT or X-ray, abdominal MRI and PET-CT scan are performed. All PET-CT-detected para-aortic lymph nodes will be described and registered per region. In the surgical staging group, all PALNs will be excised, described and registered per region in order to correlate radiological, surgical and histological findings.

### Control group

Patients in the control group will receive treatment according to the current guidelines, i.e. treatment with regards to PALN status will be based on PET-CT.

### Radiotherapy and adjuvant chemotherapy

All patients will be treated with both external beam radiotherapy (EBRT) and brachytherapy. The choice for applying extended field radiotherapy will be based on surgical staging or PET-CT, according to the results of the study arm. Concomitant chemotherapy will consist of 5 cycles of weekly cisplatin (40 mg/m2), coinciding the first dose of chemotherapy with the first dose of radiotherapy.

### Main study parameters and analysis

The main study parameters are the safety and feasibility of para-aortic surgical staging. The feasibility will be assessed by registering a proportion of included patients amongst all eligible patients. We will assess the safety by calculating means with 95% confidence intervals (CI) for length of surgery, number of complications per Clavien-Dindo category (Appendix 1), amount of blood loss and number of adverse events which will be reported using the Serious Adverse Event Report (SAE) form (Appendix 2) [23]. Also, mean nodal yield with 95% CI after para-aortic lymphadenectomy will be presented and compared to results found in other studies in order to assess completeness of lymphadenectomy.

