### Secondary study parameters and analysis

Although this is a phase 2 trial, we will also register secondary outcome parameters such as (progression-free) survival and quality of life as they are also aspects of safety. The incidence of advanced stage cervical cancer is quite low in the Netherlands. Including these secondary parameters will make it possible to enter these patients into a subsequent phase 3 trial, if the current PALDISC study shows that such a phase 3 study is indeed necessary. Decision on the necessity of a phase 3 trial will depend on whether surgical staging of PALN in advanced stage cervical cancer is deemed safe, feasible and necessary in comparison with the performance of current PET-CT imaging.

The proportion of changed initial treatment plans and diameter of metastases will be documented and presented. Data on sensitivity, specificity and negative and positive predictive values of MRI, PET-CT and surgical staging will be documented in 2 × 2 tables; estimates will be provided with 95% CI.

Time to treatment will be measured in days from the day of randomization until start of chemo radiation. Difference in treatment delay between the arms, due to surgical intervention and histological analyses, will be presented using a Kaplan-Meier curve with the corresponding medians and 95% CI. Rate differences and 95% CI for mortality and morbidity during follow-up will be calculated and presented in a table.

The analysis of progression-free survival and overall survival will be based on and presented in a Kaplan-Meier curve with corresponding hazard ratio and 95% CI. Means and range in reported quality of life will be reported using the Dutch versions of the European Organisation for Research and Treatment of Cancer (EORTC) Core Questionnaire, the QLQ-C30 version 3.0 and the supplemental cervical cancer-specific module, the QLQ-CX24 [24, 25]. The difference in quality of life between the arms will be presented as a mean difference with 95% CI.

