### Sample size calculation, data monitoring and premature termination of the study

We will include 15 patients in each arm for this phase II study. There will be no formal data-safety monitoring board due to the relatively small number of patients (*n* = 15) in the intervention arm. However, due to the nature of this intervention and possible risk related to the intervention, we have installed an independent expert to ensure the safety and ethics. After each serious adverse event, which may in any way be related to the para-aortic lymphadenectomy, all inclusions and planned interventions at all centres will be stopped immediately. All principle investigators will converge and decide whether it is ethical to resume inclusion after the serious adverse event has abated or until a stable situation has been reached. All meetings and decisions will be documented. Each conclusion will be submitted to the independent expert for an independent assessment on safety and ethics. The trial will only resume after both the principle investigators and independent expert agree that safety and ethical criteria are being met. An independent monitor will check all centres on informed consent, adherence to the in- and exclusion criteria, reporting of all adverse events and full source document verification. The monitor will audit after the first three included patients and then yearly or after every 10 included patients.

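### Complications per Clavien-Dindo category in 15 operated patients are summarised as a mean with 95% CI, which can mislead for uncommon grades; the proportion of patients affected with an exact interval would be better

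*Protocol article*

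**What the plan says.** The Protocol article, under Main study parameters and analysis, sets out the safety assessment: "We will assess the safety by calculating means with 95% confidence intervals (CI) for length of surgery, number of complications per Clavien-Dindo category". Blood loss and the adverse event count complete the same list. The Methods/design paragraph of the abstract gives the same plan for the primary outcomes: "calculating means with 95% confidence intervals for duration of surgery, number of complications, blood loss, nodal yield after para-aortic lymphadenectomy", together with treatment delay.

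The size is fixed under Sample size calculation, data monitoring and premature termination of the study: "We will include 15 patients in each arm for this phase II study". Only the intervention arm has the surgery, so the complication summary rests on at most 15 patients.

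Three further statements bear on the point:

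- The adverse event count is described as "number of adverse events which will be reported using the Serious Adverse Event Report (SAE) form".
- The independent monitor is to check "reporting of all adverse events and full source document verification".
- Among the secondary analyses: "Rate differences and 95% CI for mortality and morbidity during follow-up will be calculated and presented in a table".

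The article names no interval method for any of these and gives no expected complication rate. Risk assessment calls the risk moderate, without a figure.

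**The concern.** Operating time, blood loss and nodal yield are measured quantities, and a mean with a confidence interval is a reasonable summary of them. Complications per grade in 15 patients are counts, and in the less common grades they are likely to be zero or one. A mean with a t or normal interval behaves badly there. With no events the standard deviation is zero and the interval shrinks to a point. With one to three affected patients the lower limit is negative and the upper limit lies below the exact one.

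A mean count also does not say how many patients were affected. Three events in one patient and one event in each of three patients both give 3/15 = 0.20 per patient, yet the proportions affected are 1/15 = 6.7% and 3/15 = 20%.

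What is at stake is the use made of the result. Under Secondary study parameters and analysis, the decision on a phase 3 trial depends partly on whether the surgery is judged safe, and the Discussion leaves that decision to a group of experts. An interval of 0 to 0 for a severe grade would give those experts false reassurance.

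**Working it through.** **Inputs**

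- n = 15 operated patients (sample size section), taking it that all patients allocated to surgery are operated on.
- Two-sided 95% confidence level.
- Interval type: not stated. The t interval is taken as the ordinary reading of a mean with 95% CI; the normal interval (1.96) is shown where it differs.
- Complication rate: not stated. True rates of 1% to 40% per category are an assumption.

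**The article's own figures**

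The 15 per arm comes with no inputs, so it cannot be reproduced. The only small-sample intervals in the article are those quoted for PET-CT in 16 patients: 50% (7–93%) and 83% (52–98%). Inferring 2/4 and 10/12 from n = 16, Clopper-Pearson gives 6.8–93.2% and 51.6–97.9%, which match. The normal interval gives 1–99% and 62–104%, which do not. The evidence the article cites is thus consistent with exact limits.

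**Intervals for x affected patients out of 15**

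For 0/1 data, p = x/15, s² = 15·p(1−p)/14, and the t interval is p ± 2.145·s/√15.

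- x = 0: s = 0, so the interval is 0 to 0. The exact upper limit is 1 − 0.025^(1/15) = 21.8%.
- x = 1: p = 0.0667, s = 0.258, s/√15 = 0.0667, half-width 2.145 × 0.0667 = 0.143.

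| Affected | t interval | Clopper-Pearson |
|---|---|---|
| 0/15 | 0 to 0 | 0 to 21.8% |
| 1/15 | −7.6% to 21.0% | 0.2% to 31.9% |
| 2/15 | −6.2% to 32.8% | 1.7% to 40.5% |
| 3/15 | −2.9% to 42.9% | 4.3% to 48.1% |

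**Coverage of the nominal 95% t interval**

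Coverage is the sum, over all x whose interval contains the true rate π, of the binomial probability of x. The chance of a 0-to-0 interval is (1 − π)^15; at 5% this is 0.95^15 = 0.463.

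| Assumed true rate | Chance of 0 to 0 | t coverage | Clopper-Pearson coverage |
|---|---|---|---|
| 1% | 86.0% | 14.0% | 99.0% |
| 2% | 73.9% | 26.1% | 99.7% |
| 5% | 46.3% | 53.6% | 99.5% |
| 10% | 20.6% | 79.2% | 98.7% |
| 15% | 8.7% | 90.9% | 98.3% |
| 20% | 3.5% | 96.1% | 98.2% |
| 30% | 0.5% | 94.9% | 98.0% |
| 40% | below 0.1% | 96.4% | 98.5% |

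At low rates nearly all the loss comes from the zero-event samples: at 5%, 46.3% + 53.6% = 99.9%. With 1.96 in place of the t quantile, coverage at 20% is 81.5%.

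**Several events per patient**

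With Poisson counts (200,000 simulated samples of 15), t coverage is 25.8%, 52.8% and 77.5% at means of 0.02, 0.05 and 0.1 events per patient, and 93% to 95% at means from 0.2 to 2. The pattern is the same.

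**The case against.** The strongest objection is that the article names no interval. The collapse to 0 to 0 and the coverage figures follow only from a t or normal interval. An exact Poisson interval for the mean with no events in 15 runs from 0 to 0.246 per patient, and the choice could be made in an analysis plan that is not shown. This stands in part, and the figures above are conditional on it. But the article applies one phrase to operating time, blood loss and complication counts alike, so the t or normal reading is the natural one. Even an exact interval for a mean would not show how many patients were affected.

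Second, the rates are assumed, and the problem fades for common categories. This stands: from about 20% upward the t interval is close to nominal.

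Third, a reader might infer that safety rests on this mean alone, or that the interval would lead the trial to declare safety. The documents do not support that. The mean is one of several primary safety measures, no rule ties a conclusion to a confidence limit, inclusion stops for review after each possibly related serious adverse event, and experts take the final decision. The secondary rate differences for morbidity also help, although they are secondary and name no interval method.

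Fourth, a reader might infer that adverse events are captured only on the SAE form, so that non-serious ones are lost. The text does not say only. Complications are counted per Clavien-Dindo category without a grade cut-off, and the monitor checks reporting of all adverse events. What remains is that the passage names no other form for a count that should include non-serious events.

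**Conclusion.** The point holds for uncommon complication categories. The article itself fixes a mean with 95% CI for sparse counts in 15 patients, and a clearer and safer summary is available at little cost. On the ordinary t or normal reading, a category without events would be shown as 0 to 0 when the data allow up to 21.8%. Coverage would be about 26%, 54% and 79% at assumed rates of 2%, 5% and 10%, and about nominal for the t interval from 20% upward. The size therefore rests on two assumptions the article does not settle: the interval type and the event rate. Low rates are most plausible for the severe grades, which matter most for judging safety. The loss of information on patients affected holds whichever interval is used.

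The adverse event wording is a minor ambiguity and not evidence of under-capture.

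Trial status reports the trial cancelled after five enrolments. The point still matters because the article hopes other centres will take up such a trial and may reuse this plan.

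**What to change.** In the abstract (Methods/design) and under Main study parameters and analysis, take complications out of the list of means and state instead:

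- the number and proportion of operated patients with at least one complication of any grade, and with at least one of Clavien-Dindo grade III or higher, each with a Clopper-Pearson 95% CI;
- a listing of all complications by grade, without a mean.

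Keep means with 95% CI for duration of surgery, blood loss and nodal yield.

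As a minor clarification, add one sentence under Main study parameters and analysis saying how non-serious adverse events are recorded and whether they enter the adverse event count.

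The cost is a few sentences and, if non-serious events have no place on the case report form yet, one added page. The downside is wider and less favourable intervals: Clopper-Pearson is conservative here, with coverage of 98% or more at every rate tried from 1% to 40%.

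### Mean nodal yield set against other studies cannot show how many of the 15 dissections were incomplete; a per-patient, per-region count can

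*Protocol article*

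**What the plan says.** Under Main study parameters and analysis, the protocol article states that "mean nodal yield with 95% CI after para-aortic lymphadenectomy will be presented". The stated use of this figure is that it will be "compared to results found in other studies in order to assess completeness of lymphadenectomy". The article names no comparison studies and no benchmark yield. The abstract lists nodal yield among the primary safety and feasibility outcomes.

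The extent of surgery is fixed for every patient: Intervention, surgical procedure and histological analysis requires a "node by node para-aortic lymphadenectomy from the common iliac bifurcation up to the left renal vein". The text below Fig. 2 adds that "all PALNs will be excised, described and registered per region in order to correlate radiological, surgical and histological findings", and histology includes an "additional assessment on lymph node yield, node diameter and diameter of micro metastases". PET-CT-detected nodes are also registered by region.

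Under Secondary study parameters and analysis, sensitivity, specificity and predictive values of MRI, PET-CT and surgical staging are to be set out in 2 × 2 tables with 95% CIs. The Discussion treats histology as the gold standard. The article gives no rule for a patient whose dissection was inadequate.

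**The concern.** The article names a purpose, completeness, and a measure, the arm mean against outside series, and the measure does not serve the purpose. The protocol's own anatomical limits define completeness patient by patient. A mean can be held up by high counts while some patients have very few nodes. The outside comparison adds little, because the series are unspecified and the article allows open, laparoscopic and robot-assisted surgery by more than one route.

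Two things are at stake. First, completeness bears on feasibility, so a main outcome would rest on a summary that cannot reveal failures. Second, histology is the reference standard for PET-CT. Disease left in a PET-positive region can make a correct scan look like a false positive. Disease left in a PET-negative region can turn a missed metastasis into a true negative. The accuracy results feed the decision on a phase 3 trial, and the article says the data can be used to size it.

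**Working it through.** **Inputs from the article.** Operated patients: 15 ("We will include 15 patients in each arm for this phase II study"). Prevalence of para-aortic metastases: around 20%, up to 40% (Background). PET-CT sensitivity 50% (95% CI 7–93%) and specificity 83% (52–98%), from a study of 16 patients (Background). The article gives no nodal yield, no SD and no benchmark, so all yields below are assumptions.

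**1. Reproducing the stated accuracy figures.** The percentages and n = 16 fit 2/4 and 10/12 (counts inferred). Exact Clopper-Pearson limits are 6.8–93.2% for 2/4 and 51.6–97.9% for 10/12. Both match the article.

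**2. What the mean can hide (assumed yields).** Take 12 patients with 18 nodes and 3 with 3 nodes.
- Mean = (12 × 18 + 3 × 3)/15 = 225/15 = 15.0
- SD = √[(12 × 3² + 3 × 12²)/14] = √(540/14) = 6.21
- Half-width = 2.145 × 6.21/√15 = 3.44, so the 95% CI is 11.6 to 18.4

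The same mean could come from 15 uniform dissections. The proportion with the higher yield is 12/15 = 80%, exact 95% CI 52–96%, which the mean does not show.

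**3. Sensitivity to the assumed yields.** In 20,000 simulated trials of 15 patients for each setting, complete dissections averaged 12 (SD 5), 15 (SD 6) or 20 (SD 8) nodes and an incomplete one yielded 2. The benchmark was the complete-dissection mean. The share of trials in which the upper limit of the 95% CI still reached the benchmark was:

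| Incomplete, of 15 | Share reaching benchmark |
|---|---|
| 0 | about 97% |
| 1 | about 95% |
| 2 | 90–91% |
| 3 | 82–83% |

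The comparison barely separates a trial with no incomplete dissections from one with three.

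**4. Effect of one misclassified patient.** Expected node-positives: 15 × 0.20 = 3 to 15 × 0.40 = 6. In each case one truly positive patient is recorded as node-negative.

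| Case | Sensitivity | Specificity |
|---|---|---|
| 3 positives, no error | 2/3 = 67% | 10/12 = 83% |
| PET-positive patient missed | 1/2 = 50% | 10/13 = 77% |
| PET-negative patient missed | 2/2 = 100% | 11/13 = 85% |
| 6 positives, no error | 3/6 = 50% | 7/9 = 78% |
| PET-positive patient missed | 2/5 = 40% | 7/10 = 70% |
| PET-negative patient missed | 3/5 = 60% | 8/10 = 80% |

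With 3 positives, a missed PET-positive patient lowers specificity by 83.3 − 76.9 = 6.4 points.

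**The case against.** The strongest reply is that the weakness lies in one summary sentence, not in the design. The dissection limits are the same for everyone, an experienced team operates, and yield and nodes are recorded by region with the stated aim of correlating imaging, surgery and histology. With 15 patients, a PET-positive region that returned no nodes could be found from those records. This stands, and it is why the remedy is cheap. It does not make the arm mean a measure of completeness.

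A reader might infer that the 2 × 2 tables will count incomplete dissections as node-negative. The article does not say so. It gives no rule either way, and the handling of an inadequate reference test may be set out in the full protocol or analysis plan, which are not shown. Intention to treat with no visible indeterminate category makes that classification possible, not certain.

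A reader might also infer that the accuracy results would be badly distorted. The yields in the example are invented, and a 6-point shift lies well inside the article's own 52–98% interval for specificity. Accuracy is a secondary parameter, the yield comparison carries no pass/fail threshold, and the trial was cancelled with five patients enrolled. These points limit the weight of the concern. But the protocol was published partly to interest other centres in such a trial, so the measure may be reused.

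**Conclusion.** The point holds in a limited form. The only completeness assessment that the article states is the arm's mean yield against unspecified studies, and that summary cannot show how many of the 15 dissections were incomplete. This rests on the stated text and needs no assumed figure. The 15.0 (11.6 to 18.4) example and the simulation only illustrate it, with yields that are not the article's.

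The effect on accuracy is conditional: an incomplete dissection with negative histology could be tabulated as node-negative. If that happened once, in a PET-positive patient with disease, specificity would fall by about 6 points at 20% prevalence (8 points at 40%: 7/9 to 7/10), and sensitivity would lose one of about 3 to 6 positives. The change is worth making because it is cheap.

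**What to change.** **Main study parameters and analysis.** Report the number and proportion of operated patients in whom every region within the protocol's dissection limits, including each PET-positive region, was recorded as dissected. Give an exact 95% CI and show the nodes retrieved per region. Use the record of dissection as the criterion, not the retrieval of a node: one node does not prove that a region was cleared, and a cleared region may hold none. Give nodal yield as median and range, or as individual values, and keep the comparison with other studies as descriptive only.

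**Secondary study parameters and analysis.** Keep the accuracy table for all operated patients as the main one. Add a sensitivity table restricted to complete dissections, labelled as possibly selective because incompleteness may be related to difficult disease.

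**Cost.** Some wording and one extra table from data already planned by region. If the form lists only retrieved nodes, one yes/no item per region is needed. The extra table will have a smaller denominator, possibly with fewer than the 3 expected positives, and regions that contain no nodes may still be misclassified. Surgery and treatment rules do not change.
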